#### Secondary outcome measures

Secondary outcome measures include standardized self-report questionnaires assessing cognitive complaints (CSC-W DV) [34], work ability (WAI) [35, 36], work functioning (WRFQ) [37], absenteeism and presenteeism (iPCQ) [38], need for recovery after a working day (VVBA) [39, 40], and health-related quality of life (SF-36) [41].

#### Mediation and moderating measures

Fatigue (SF-36) and coping (CERQ) are considered mediators and will be assessed through self-report questionnaires [42, 43]. Neuropsychological functioning is considered a moderator and will be measured using a self-administered online neuropsychological test battery (ACS) [44]. Other moderators are work involvement (WIS) [45], job characteristics (JCQ) [46], depression and anxiety (HADS) [47], and treatment utilization (Log-data of the online program).

### Cost-effectiveness

An economic evaluation will be conducted alongside the trial to evaluate costs and patient outcomes of implementing the online cognitive rehabilitation program. Both cost-utility analysis (CUA) and cost-effectiveness analysis (CEA) will be conducted. Quality-adjusted life years (QALYs) will be measured using EQ-5D-5L [48]. Intervention costs will be calculated, including health professional labor (time spent on treatment per patient), staff training, administration, and material costs. Unit prices (or appropriate tariffs) will be multiplied by volumes of use, following the Dutch costing guidelines [49]. Health care costs will be assessed using self-reported questionnaires about participants’ use of health care services (e.g., general practitioner (GP), medical specialist, paramedical care). Productivity costs will be administered by questionnaires reporting on productivity losses due to sickness absence from work (absenteeism) and health-related diminished productivity at work (presenteeism). Presenteeism and sickness absence will be administered with the Productivity Costs Questionnaire (iPCQ). This questionnaire includes three questions for measuring absenteeism and three questions identifying the proportion of presenteeism [38]. Full working days lost because of presenteeism are calculated according to following formula: *P* = (*E* − *A*)∗ *p*, in which *E* is the total working days, *A* is sickness absence days, and *p* is the proportion of lost work performance due to presenteeism. Productivity loss will be valued using age-, gender-, and/or education-specific price weights.

### Process evaluation

A process evaluation will be conducted to evaluate strategy fidelity, satisfaction, and facilitators or barriers for implementation of the cognitive rehabilitation program. Six components will be assessed, namely, recruitment, reach, dosage, differentiation, implementation, and experiences (of both participants and therapists). We define recruitment as the result of all procedures to recruit eligible cancer survivors for participation. Reach is defined as the percentage and characteristics of persons who receive the intervention program. The extent to which the participants actually were exposed to the intervention will account as treatment dosage. Furthermore, differentiation is regarded as the identification of unique and essential intervention features. Implementation refers to the qualitative aspects of the manner in which the intervention program was delivered. Participants’ and therapists’ experiences with the intervention activities will be evaluated. To gather data for the process evaluation, periodic self-report questionnaires for participants will be provided at the end of every module (for an overview of modules, see Table 1) and at T1. A self-report questionnaire for the therapists will be provided at the end of the trial.

### Sample size calculation

This longitudinal study design will allow for testing of the main effect of the intervention over time, with the GAS score as the primary outcome measure. With a sample size of 65, and an alpha = 0.05, the study will allow for an attrition rate of approximately 20% and have 80% power to detect an effect size of *f* = 0.2 (equivalent to Cohens *d* = 0.4) for the main effect of the intervention between both the basic and extended cognitive rehabilitation treatment group versus the waitlist control group (first hypothesis). To perform subgroup analysis, used to test our second hypothesis, sample size should be inflated fourfold [50]. Therefore, we strive for a sample size of 261, with 87 patients in each group.

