### Recruitment and randomization

Cancer patients will be identified through the Netherlands Cancer Registry and recruited via treating physicians of several (university) hospitals in the Netherlands. Potentially eligible patients will receive a personalized letter from their treating physician, informing them about the study and the cognitive rehabilitation program. Patients will be asked to respond via post (response card), email, or phone whether or not they are interested in participation. In case a patient does not respond, a reminding letter will be sent after 3 weeks. Patients who express interest in participation will receive a phone call from the study team for further screening (e.g., a check of their employment status) and to provide additional information about the trial. Patients will be invited by e-mail to complete the baseline measurement (i.e., an online questionnaire and an online neuropsychological assessment) in case they fulfill all criteria, are motivated, and are willing to comply to the trial procedures. After completion of this baseline measurement, a session (face-to-face or using videoconference) with a therapist (e.g., neuropsychologist, occupational therapist) will be planned to discuss outcomes of the neuropsychological assessment, followed by collaborative treatment goal setting.

Upon receipt of all baseline information and after the session with the therapist, patients will be randomly allocated to the basic intervention arm (*N* = 87), the extensive intervention arm (*N* = 87), or the waitlist control group (*N* = 87), using randomized design in the computerized program ALEA. Minimization will be applied for the presence of cognitive impairment on the neuropsychological assessment to equalize group sizes. Blinding of participants and professionals is not possible for this type of intervention. Further, blinding for assessment is not applicable since measurements will be computer-based. A flow diagram of the recruitment procedure is outlined in Fig. 1. Figure 2 shows a schedule of enrolment, interventions, and assessments.

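### The claim that 65 patients give 80% power at d = 0.4 mislabels the test and effect size, and the fourfold step to 261 leaves hypothesis 2 at low power for that effect

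*Protocol article*

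**What the plan says.** All of this is in the protocol article. Under Sample size calculation the base claim is "With a sample size of 65, and an alpha = 0.05, the study will allow for an attrition rate of approximately 20" per cent and "have 80% power to detect an effect size of *f* = 0.2 (equivalent to Cohens *d* = 0.4"). The contrast is given as "for the main effect of the intervention between both the basic and extended cognitive rehabilitation treatment group versus the waitlist control group (first hypothesis"). The section opens: "This longitudinal study design will allow for testing of the main effect of the intervention over time, with the GAS score as the primary outcome". It names no test family and no within-person correlation.

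The step to the final number is: "To perform subgroup analysis, used to test our second hypothesis, sample size should be inflated fourfold". The result is 261, or 87 per arm, which agrees with the three-arm allocation under Recruitment and randomization.

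Three other places bear on the calculation:
- The Background defines hypothesis 2 as extensive versus basic among patients with cognitive impairment.
- Statistical analysis plans to test moderation by impairment, and regards effects of about 0.5 as clinically relevant and 0.8 as large.
- Primary outcome measure says that goals are set at T0 and that attainment is rated at T1 and T2.

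**The concern.** A comparison of two means at d = 0.4 usually needs about 100 analysed patients per arm for 80% power. A total of 65 over three arms, with a fifth lost, is far below that. Either the test or the effect size must therefore differ from what the section states.

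The error matters because the base number is then multiplied by four to justify 261, and the stated reason for 261 is hypothesis 2. If the base does not have 80% power at d = 0.4, the multiplied number does not carry 80% power to the subgroup question. A null subgroup result could then be read as coming from an adequately powered test.

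**Working it through.** **Inputs.** From Sample size calculation: 65, alpha 0.05, about 20% attrition, 80% power, f = 0.2 called d = 0.4, a factor of 4, 261 in total and 87 per arm. Assumed: a two-sided test; a within-person correlation r (0.5 unless stated); an impaired share of 30 to 50%, which the protocol does not give.

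**Is 65 a total or per arm?** 4 x 65 = 260, and the next multiple of 3 is 261 = 3 x 87. So 65 is a total. After 20% attrition it leaves 0.8 x 65 = 52, or 17.3 per arm. The planned 261 leaves about 209, or 0.8 x 87 = 69.6 per arm.

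**Reproducing the 65.** For a repeated-measures group-by-time interaction with m occasions, the noncentrality is f² x N x m / (1 - r).
- 3 groups, 3 occasions: 0.04 x 52 x 3 / 0.5 = 12.48 on 4 and 98 df, power 79.8%.
- 2 groups, 2 occasions: 0.04 x 52 x 2 / 0.5 = 8.32 on 1 and 50 df, power 80.7%.

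Then 52 / 0.8 = 65. Of the between-arm comparisons tried, only this interaction gives the stated figure.

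**What f = 0.2 means in that test.** Take control means (0, 0, 0) and both programmes (0, d, d). The SD of the interaction effects is then 2d/9 = 0.222d, so f = 0.2 gives d = 0.9. In the 2 x 2 case it is d/4, so d = 0.8. A true d = 0.4 is f = 0.089 or 0.10, and power with 52 completers falls to 20% or 29%.

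**The claim as worded (main effect, 52 completers).**

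| Test | Power |
|---|---|
| Arm versus arm, d = 0.4 | 21% |
| Programmes pooled versus control, d = 0.4 | 27% |
| Three-group F test, f = 0.2 (noncentrality 0.04 x 52 = 2.08) | 22% |
| Repeated-measures between-group effect, f = 0.2, 3 occasions (0.04 x 52 x 3 / 2 = 3.12) | 32% |

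Reading 65 as per arm gives 62%, or 52% with 52 completers per arm.

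**Fit with the endpoint.** Goal attainment is rated only at T1 and T2, so a three-occasion interaction lacks a rated baseline. On T1 and T2 alone, a constant programme benefit produces no group-by-time interaction at all.

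**Hypothesis 1 at 261 (69.6 analysed per arm, d = 0.4).** Averaging T1 and T2 divides the SD by the factor that turns 0.4 into 0.4 / sqrt((1 + r)/2): 0.462 at r = 0.5 and 0.422 at r = 0.8.

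| Contrast | One time point | Mean of T1 and T2 (r = 0.8 to 0.5) |
|---|---|---|
| Pairwise | 65% | 69 to 77% |
| Pooled | 77% | 82 to 88% |

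**Hypothesis 2 at 261 (d = 0.4).** With impaired share p, each arm has 69.6p impaired patients: 20.9 at 30% and 34.8 at 50%. The interaction has SE = sqrt(2/(69.6p) + 2/(69.6(1 - p))), which is 0.370 at 30% and 0.339 at 50%. Interaction power uses the normal approximation.

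| Test | 30% impaired | 50% impaired |
|---|---|---|
| Interaction of 0.4, one time point | 19% | 22% |
| Extensive versus basic in impaired, one time point | 24% | 38% |
| Same comparison, mean of T1 and T2, r = 0.5 | 31% | 48% |

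**Why the fourfold step does not help.** With half the patients impaired, the interaction contrast has four times the variance of the main contrast. Multiplying N by four therefore keeps the base power for an interaction as large as the main effect. The base is 21% arm versus arm at 52 completers, and the interaction at 209 completers has 22%.

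**The case against.** **The 65 is not an arithmetic slip.** This stands. It follows from a recognisable calculation, and the section speaks of an effect over time in a longitudinal design, which is loosely the language of an interaction. The defect is that an interaction f has been called a main effect and equated with d = 0.4. A condensed article may leave the test family and correlation to the full protocol, so their absence alone is no finding. The false equivalence is stated in the text, however.

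**A reader might infer that the trial has only 20 to 30% power for hypothesis 1, or that it is adequately powered for neither hypothesis.** The documents do not support that. The trial enrols 261, and 65 is an intermediate number. If the contrast is read as both programmes pooled against waitlist and T1 and T2 are averaged, power at d = 0.4 is 82 to 88%. At 0.5, the effect the protocol calls clinically relevant, pairwise power at one time point is about 84%.

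**The hypothesis 2 figures rest on an assumed impaired share.** This also stands, and they must be read as a range. If the interaction f = 0.2 with r = 0.5 is accepted, extensive versus basic in impaired patients reaches 80% at a 30% share. But for two arms and three occasions the SD of the interaction effects is 0.5 x sqrt(2/9) x d = 0.236d, so that f means about 0.85 SD, not 0.4.

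**Conclusion.** The power statement is wrong as written. At d = 0.4, two-sided alpha 0.05 and 52 completers, power is about 21% pairwise and 27% pooled. It is 22 to 32% for the omnibus or repeated-measures between-group test at f = 0.2. The 65 comes out of a group-by-time interaction in which f = 0.2 stands for 0.8 to 0.9 SD, a test that suits the rating schedule of the endpoint poorly.

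The consequence falls on hypothesis 2. At 261 with 20% attrition it does not have 80% power at d = 0.4 under any impaired share from 30 to 50%, whether tested as an interaction or within the subgroup. Hypothesis 1 is somewhat short of 80% pairwise and close to or above it pooled. It would be wrong to call the trial as a whole underpowered for hypothesis 1.

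The direction of these conclusions is firm. The exact hypothesis 2 figures depend on the assumed share and correlation.

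**What to change.** Keep 261. In Sample size calculation, delete the statement that 65 patients give 80% power at d = 0.4, and delete the fourfold derivation. In their place:

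- Name the test for each hypothesis, and say whether hypothesis 1 is pairwise or pooled.
- State power or the detectable difference at 87 per arm with 20% attrition, with the T1-T2 correlation and the impaired share declared as assumptions. At 80% power and one time point, the detectable difference is about 0.48 SD pairwise for hypothesis 1. For extensive versus basic in impaired patients it is about 0.68 SD at 50% impaired and 0.89 SD at 30%.
- Label hypothesis 2 as low-power.

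This is a rewording. It needs no extra patients and no change to design, endpoint or analysis. The only downside is a less favourable stated power.

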### Statistical analysis

All data will be pseudo-anonymized prior to data analyses. The data set will not contain any personal identifiers. The information that is given online by patients is accessible to the study staff only, via a secured code. Means and SDs will be presented for continuous, normally distributed variables, and median and ranges for non-normally distributed variables. First, analyses will be performed to evaluate the comparability of the three study arms (i.e., the basic and extensive cognitive rehabilitation groups and the waiting list control group) at study entry, in terms of sociodemographic and clinical characteristics. ANOVA tests or appropriate non-parametric statistics will be used, depending on the level of measurement. If, despite the stratified block randomization procedure, the groups are found not to be comparable on one or more background variables, then those variables will be employed as covariates in subsequent analyses.

In this study, GAS will be used as the primary study endpoint, evaluating between-group differences over time in GAS scores. The GAS scores will be calculated according to published scoring algorithms (see the “Methods/design” section). To evaluate intra-individual differences in the trajectory of change over time for the primary outcome, we will use a growth curve modeling approach with random intercept and slope. This approach takes into account the within- and between-person variability and deals adequately with missing data [51]. Both linear and quadratic effect of time will be modeled to determine if an initial improvement or deterioration in the outcome was followed by a deceleration of this change over time. Appropriateness of the final model (with or without quadratic effect) will be determined based on model fit statistics: the Bayesian information criterion [52] and the Akaike information criterion [53]. In all analyses, the control group will be the reference group. Furthermore, moderation analysis will be conducted to determine whether the interventions have a differential effect among the subgroups classified as cognitive impaired yes or no (measured by ACS) at baseline. Baseline differences will be accounted for in the model. In case of non-ignorable dropout, we will correct the model for different patterns of missing values [54]. All analyses will be done on an intention-to-treat basis. Furthermore, as a secondary analysis, per-protocol analyses will be performed on patients who met criteria for minimal compliance (i.e., at least 4 logins into the online program) with the intervention(s). Differences in mean change scores over time between the intervention groups and the control group will be accompanied by effect sizes. Effect sizes of 0.2 are considered small, 0.5 moderate, and 0.8 large [55]. Effect sizes of approximately 0.5 are considered to be clinically relevant [56].

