#### Primary outcome measure

The primary outcome for this study will be individually defined work-related treatment goals, using the 6-point Goal Attainment Scale (GAS) on personal outcome (− 3, achievement of the goal after training is worse; − 2, achievement of the goal is the same; 1, partial achievement of the goal; 0, achievement of the goal; 1, exceeding the goal; and 2, greatly exceeding the goal) [33]. Patients will formulate three treatment goals and define the six outcome levels at baseline, in collaboration with their therapist. Attainment of the goals is measured in a standardized way, i.e., an overall GAS *T*-score will be computed for each participant on the basis of aggregated GAS scores involving attainment of multiple personal treatment goals, according to a summary scoring algorithm that calculates the extent to which patients’ goals are met.
$$ T=50+\frac{10\sum {w}_i{x}_i}{{\sqrt{\left(1\hbox{-} \rho \right)\kern0.5em \sum {w_i}^2+\rho \left(\sum {w}_i\right)}}^2} $$

*T* is the composite score, *w*_*i*_ is the weight assigned to goal_*i*_ (based on the patients prioritization), *x*_*i*_ is the original score for goal_*i*_ ranging from − 3 to + 2, and *ρ* is the estimated correlation between goal scores. The *T*-score has a mean of 50 and a standard deviation of 10. *w*_*i*_ is considered as equally relevant for each goal and thus assigned 1. Based on previous studies, correlation between the goal scores is constant and can be set at 0.3 [33]. Goals will be set at baseline (T0), and evaluated by patients (of all study arms) in collaboration with the cognitive therapist at T1 and T2. Due to practical reasons, this scoring of the level of attainment will be done by telephone. An independent assessor will perform quality checks on the use and scoring of GAS during the initial phase of the trial, to assure fidelity of the GAS-protocol.

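### The statement that the growth model handles missing data does not hold for patients with no GAS score at either T1 or T2, who add nothing to the primary contrast

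*Protocol article*

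**What the plan says.** The section Statistical analysis makes GAS the primary endpoint and compares the arms with a growth curve model that has a random intercept and a random slope. It says that this approach "deals adequately with missing data", and later: "All analyses will be done on an intention-to-treat basis". The section has two further provisions. If dropout turns out to be non-ignorable, the model will be corrected for missingness patterns. Baseline differences will also be taken into account, and background variables become covariates when the arms are found not to be comparable on them.

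The section Primary outcome measure describes the scoring: "Goals will be set at baseline (T0), and evaluated by patients (of all study arms) in collaboration with the cognitive therapist at T1 and T2". It is done by telephone. On the content of the score: "Patients will formulate three treatment goals and define the six outcome levels at baseline". Level −2 is defined as "achievement of the goal is the same", the weight "is considered as equally relevant for each goal and thus assigned 1", and the correlation between goals is set at 0.3. The Abstract lists baseline among the measurement times of the primary outcome, but Primary outcome measure describes only goal setting at that visit.

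The section Sample size calculation says that "the study will allow for an attrition rate of approximately 20" per cent. It does not say how much of this falls before T1.

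**The concern.** A likelihood-based mixed model supports a missing-at-random assumption by using what was observed of the same patient's outcome. For the questionnaires there is a real T0 score, so even a patient lost early contributes something. GAS has no varying baseline. A patient never scored has either no outcome row or a row holding a constant, so the model learns nothing from that patient about the arm difference.

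For this group the intention-to-treat statement is then not met as written: the primary contrast rests on patients with at least one GAS score. If those lost early in the programme arms are disproportionately people who did little with the programme, the estimate moves from the effect of offering the programme toward the effect in those who persisted. This can happen even when the loss could be explained by data that the trial collects but the stated model does not use.

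**Working it through.** **1. The plan's attrition figure.** The base sample size of 65 is reproduced for a group-by-time interaction with f = 0.2, alpha 0.05, 80% power, two groups, two measurements and an assumed within-person correlation of 0.5. That requires 52, and 52/0.8 = 65. Then 4 × 65 = 260, close to the stated 261 = 3 × 87. The correlation is not stated; at 0.3 to 0.7 the figure after attrition runs from 89 to 40. The match does not bear on the point below. It shows only that the attrition allowance concerns numbers of patients, not bias.

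**2. The implied T0 score.** Inputs from Primary outcome measure: three goals, weights 1, correlation 0.3, no change = −2.

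T = 50 + 10 × (−6) / √(0.7 × 3 + 0.3 × 9) = 50 − 60/√4.8 = 22.6

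This holds for every patient, so the variance at T0 is zero.

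**3. What a patient with no T1 and no T2 score contributes.** A trial of 261 was simulated with assumed means and variances and random loss before T1. In the draw used, 222 patients had a GAS score and 39 had none.

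- T1 and T2 rows only: the estimates are identical whether or not the 39 are in the file.
- Constant T0 = 22.6 added for everyone, time categorical: the four arm-by-time estimates (5.25, 4.72, 6.13, 3.90) are identical with and without the 39. Only the standard errors change, from about 1.62 to about 1.53. That gain is an artefact of zero-variance rows.
- Constant T0 added, linear time with random slope: the slopes barely move (2.76 against 2.77; 1.69 against 1.73), the intercept variance goes to the boundary, and the fit that includes the 39 does not converge.

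**4. The other provisions.** Correction for missingness patterns needs a mean for each pattern. The pattern with no GAS score has no outcome data, so its mean needs an outside assumption, and none is given. Covariates can make the available-case analysis valid if loss depends only on them and on arm, but the plan selects them for imbalance between arms, not for predicting loss.

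**5. How many.** 0.20 × 261 = 52 if all attrition falls before T1 and no one lost there is scored at T2. If half falls before T1, the figure is about 26.

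**6. Possible size of the bias.** Assume that, in a programme arm, 20% are non-users with no effect and 20% have no GAS score, and that waitlist loss is unrelated to outcome. Let δ be the effect in users, so the effect in all randomised is 0.8δ. Let s be the share of non-users among those lost.

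Ratio = [1 − (0.20 − 0.20s)/0.80] / 0.80

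| s | Non-users among those scored | Effect in those scored | Ratio | If the true effect is 0.40 SD |
|---|---|---|---|---|
| 0.20 (as in the whole arm) | 0.16/0.80 = 0.200 | 0.800δ | 1.00 | 0.40 |
| 0.50 | 0.10/0.80 = 0.125 | 0.875δ | 1.09 | 0.44 |
| 1.00 | 0 | δ | 1.25 | 0.50 |

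A second illustration uses T points. Suppose early dropouts in every arm would have scored g points below those who stay. The bias is then (loss in programme arm − loss in waitlist) × g. With 20% against 10% loss and g = 5 to 10, it is 0.5 to 1.0 points, against a target of 4 (0.4 × SD 10). With equal loss it is 0.

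**The case against.** Much can be said for the plan as written.

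- It does not rely on the growth model alone. It foresees pattern correction and adjustment for baseline differences. This stands as a description of the plan, but neither provision supplies the missing mean (step 4).
- A reader might infer that the model gives GAS no protection at all. The document does not support that. A patient scored at T1 and lost before T2 has an earlier score of their own, which the likelihood uses, and a patient who misses T1 but is scored at T2 also stays in.
- A reader might infer that everyone who stops the online programme leaves the analysis. That does not follow. GAS is scored by telephone in all arms, separately from logins, so a non-user can still be called and scored. Nothing in the document says that those without a GAS score are mostly low users.
- Leaving patients out is not the same as bias. The analysis remains valid if early loss is unrelated to outcome given arm and the modelled covariates. The bias is also zero if loss and its relation to outcome are the same in all arms.
- Details of imputation are commonly left to a statistical analysis plan, which is not shown. That is fair, and the point does not rest on their absence. It rests on a property that the article asserts for the primary outcome and that does not hold for one group of patients.

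**Conclusion.** The point stands in a limited form. For patients with no GAS score at T1 or T2, neither the missing-data statement nor the intention-to-treat statement holds for the primary outcome. This follows from the document's own scoring rule and needs no assumption. It does not extend to patients scored at least once, or to the questionnaire outcomes.

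The size is uncertain. About 52 of 261 is a ceiling at the planned attrition, not an expected number. The factor of 1.00 to 1.25 rests on the assumed 20% non-users, no effect in them, 20% loss in the programme arm and uninformative loss in the waitlist. A reader might take from the upper end that a true 0.40 SD will be reported as 0.50 SD, the plan's own mark for clinical relevance. That needs every lost patient to be a non-user and all attrition to fall before T1, and the document supports neither. It would be equally wrong to assume that the bias is nil.

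**What to change.** In Statistical analysis, limit the missing-data statement for GAS to patients with at least one GAS score after baseline. Then prespecify:

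- multiple imputation of the T1 and T2 GAS T-scores within arm, using T0 covariates (cognitive impairment, CSC-W DV, WRFQ, WAI, HADS), whatever T1 and T2 online questionnaires are available and, in the programme arms, the log-data;
- the primary contrast on all 261 randomised patients, with the available-case growth model reported beside it;
- that no constant T0 GAS row is entered as data.

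The later questionnaires and log-data belong in the imputation model rather than among the covariates of the primary model. They arise after randomisation, and adjusting for them would distort the treatment contrast.

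The cost is wording and some analysis work; all variables are already collected. The downside is reliance on the imputation model. The gain is limited for patients who also miss the later questionnaires, because imputation then rests on T0 data and, in the programme arms only, on log-data.
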